### Data Collection

#### Substudy A: Trajectory Analysis

The trajectory analysis will examine the experience of the FASTRACS intervention from the perspective of RECOVA-BCS and the individuals who supported them. To do so, it will explore the extent to which the intervention influenced their RTW pathway by studying its implementation, impact mechanisms, and the effects it might have produced while considering the contexts in which the intervention took place.

Each identified RECOVA-BCS, RTW supporter, and PTA will be interviewed individually. Each interview will take place at the location and using the modality chosen by the participant (face-to-face, videoconference, or telephone).

Five interview guides (Multimedia Appendix 1) were developed using a hypothetico-deductive approach, based on the methodology of the explanatory interview [38] and guided by the realist interviewing process of conceptual focusing [39]. The guides were developed from the initial FASTRACS program theory (publication forthcoming and Broc et al [23]) and its hypothesized intervention effects but were intentionally designed around open-ended and narrative questions to minimize the induction of expected responses and limit social desirability bias. This approach aims to leave sufficient space for participants to describe their lived experiences and trajectories in their own terms, while still allowing exploration of mechanisms, contextual conditions, and perceived effects related to the intervention.

These guides have been designed to meet the objectives of the intervention and are adapted to the different categories of interviewees. The open-ended questions in the guides are both narrative (to explore personal experiences) and structural (to identify the key stages). This structure is intended to capture how each participant experienced and perceived the intervention. The guides were reviewed and adjusted after the first interviews and, in line with realist evaluation principles, may continue to evolve iteratively throughout the study to further explore emerging ICAMO configurations and unresolved analytical questions. The themes of the interview guides are shown in Table 1.

**Table 1. T1:** Interview themes by participant type.

Participant	Interview guide themes
RECOVA-BCS^a^	The decision to RTW^b^ and the associated experiences Relationship to work Use and appreciation of the patient guide Support received from PTA^c^ Emotional and social support from RTW supporters Process of reestablishing contact and links with the company
RTW supporters	Medical opinion on the situation of the RECOVA-BCS (if health professional) Emotional and social support given and received Knowledge of the relationship between RECOVA-BCS and work Use and appreciation of the patient guide
General practitioner	Consultations with the patient RTW support Side effects and RTW Emotional and social support from those around the RECOVA-BCS Use and appreciation of the checklist Knowledge and use of the patient guide Professional coordination and its perceived effects
Occupational physician	The role of RECOVA-BCS in the company The RTW career path of RECOVA-BCS and the factors that hinder or facilitate it Knowledge and use of the employer’s guide Use and appreciation of the checklist Knowledge and use of the patient guide
Workplace actors	Workplace description RTW of the RECOVA-BCS Use and assessment of the employer’s guide Actions taken and resources mobilized Development of new managerial skills

a RECOVA-BCS: sample of typical cases among breast cancer survivors who completed follow-up in the FASTRACS-RCT (FAcilitating and SusTain the Return to work After breast Cancer randomized controlled trial) intervention group.

b RTW: return to work.

c PTA: program theory actor.

#### Substudy B: Professionals Delivering the Intervention

In this substudy, the experiences of professionals delivering the FASTRACS intervention will be explored to analyze its implementation. These focus groups will be organized in parallel with the semistructured interviews of substudy A and after their completion, to allow triangulation and clarification of the information collected. Each focus group will last between 1.5 and 2 hours. They will be conducted with the various categories of stakeholders involved (oncologists, clinical research associates, general practitioners, and occupational health teams).

A focus group guide was designed for each category of participants following a realist evaluation approach [40]. This guide is structured around themes relating to the experience of the intervention, the obstacles and facilitators encountered during its implementation, its integration into professional practice, and its appropriation by those delivering the intervention. In line with conceptual focusing principles, the guides may be refined iteratively throughout the study to further investigate emerging ICAMO configurations. The main themes of the guides are shown in Textbox 1.

Textbox 1.Interviewer questions guide themes for professionals delivering the intervention.
**Focus group guide themes**
· How they got involved?· Pathway of the RCT-I (breast cancer survivors who completed follow-up in the FASTRACS-RCT intervention group)· Use and appreciation of the intervention tools· Experience of the research in the context of their professional practice

To minimize hierarchical or professional power imbalances, profession-specific focus groups will be organized separately for each stakeholder category and will follow the recommendations of our participatory committee (comprising representatives of doctors and business representatives). The facilitators will actively encourage balanced participation and constructive discussion to ensure that all participants can freely express their views and experiences.

#### Substudy C: Quantitative Data

To complement the qualitative data gathered through semistructured interviews, we will extract relevant items related to intervention processes from the questionnaires completed as part of the FASTRACS-RCT [25], which are securely stored in the Ennov database. The full list of questions can be found in Multimedia Appendix 2. These questions are selected for their relevance to the analysis of key aspects of the intervention and will focus on 5 domains: personal situation, professional situation, RTW, care pathway, and the use and assessment of intervention tools.

Quantitative data management is carried out in the context of the FASTRACS-RCT by the project team ([name], [name], and PD) and is, therefore, described elsewhere [25]. This team is affiliated with *Hospices Civils de Lyon* and is, therefore, independent of the funders.

We will first jointly analyze the qualitative and quantitative data from the RECOVA-BCSs and further compare their trajectories with those of the broader FASTRACS-BCS population using embedded integration.

### Data Analysis

The realist analysis will be carried out in an extended context-mechanism-outcome configuration: ICAMO [41]. The intervention is defined as the resources and components delivered by the program (eg, patient guide, checklists, and coordination procedures). Context refers to external and individual conditions shaping the activation of mechanisms, including organizational settings, health care pathways, workplace environments, interpersonal relationships, and personal circumstances embedded within different ecological levels of the patient’s situation [42,43]. Actors are individuals or groups whose behavior or reasoning is targeted by the intervention [44]. Mechanisms are defined as changes in reasoning and reactions that bring about change [45]. Outcomes refer to the observable effects generated by these mechanism-context interactions [46].

To avoid any confusion between intervention components and mechanisms, a structured decision rule will be applied during analysis: (1) if a statement describes “what the program provides,” it will be coded as intervention; (2) if it describes “what is happening in the environment,” it will be coded as context; (3) if it describes “what actors think, decide, or do in response to resources within a context,” it will be coded as mechanism.

For example, the patient guide is an intervention component; being provided with the guide is the intervention exposure; feeling reassured or legitimized to discuss RTW with health care providers after reading it is a mechanism; and organizational support from an employer facilitating reduced working hours is a contextual condition influencing whether this mechanism is activated.

### Qualitative Analysis

A 2-phase thematic analysis of qualitative interviews:

Deductive coding processes will be applied using the initial program theory of the FASTRACS intervention (publication forthcoming), which has been previously translated into ICAMO configurations. This step will allow for the identification of key actors, intervention components, and the mapping of RTW pathways in relation to the initial theoretical propositions.Inductive coding analysis will identify the ICAMO configurations underlying the facilitators and barriers to the intervention’s effectiveness [31].

To enhance rigor, at least 2 researchers will independently analyze the transcripts before engaging in counterfactual reasoning and judgmental rationality, comparing and refining the ICAMO configurations. MAXQDA 24 software (MAXQDA) will be used to integrate and compare the entire corpus.

### Quantitative Data Integration

Quantitative data from FASTRACS-RCT surveys (collected at baseline, 4, 8, and 12 mo) will be analyzed following the prespecified statistical analysis plan [25]. In addition, subgroup analyses (eg, by socioprofessional category, age, center, and company size) will be used to test the hypotheses developed during the interviews.

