Only participants from the intervention arm will be included in the qualitative trajectory analysis, as the objective of the realist evaluation is to explore the implementation processes, mechanisms, and contextual conditions associated with exposure to the FASTRACS intervention. The study does not aim to qualitatively compare intervention and usual-care trajectories. However, experiences related to usual care, RTW barriers, and the ordinary experience of living with breast cancer and RTW have already been extensively explored during the needs assessment phase of the intervention mapping process [20]. In addition, the profession-specific focus groups conducted with professionals involved in RTW support will contribute to documenting routine professional practices and usual-care conditions experienced by women participating in the FASTRACS-RCT. Quantitative data from the FASTRACS-RCT, including participants from both intervention and usual-care groups, will further support contextualization and interpretation of the intervention-specific mechanisms identified through the realist analysis.

Triangulation of qualitative findings with quantitative data will allow the formulation of hypotheses on the implementation, underlying contexts, mechanisms, and effects that the intervention might produce on the RCT-I. Figure 1 illustrates the design of the study.

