We anticipate including approximately 20 RECOVA-BCS in individual interviews over time to gather sufficient information on how the intervention is experienced by a large diversity of profiles. This sample size aligns with qualitative and realist-informed studies. For each RECOVA-BCS, interviews will also be conducted with up to 4 individuals involved in their RTW support, including at least one PTA, allowing for the triangulation of perspectives across key actors involved in the RTW process. We expect to identify between 10 and 15 theoretical pathways (ie, the patient and 1 PTA) to maximize the diversity of RTW trajectories. However, this is an iterative process, and the reality on the ground may lead us to revise our initial sampling.

At the end of the FASTRACS-RCT, deviant and crucial cases [36] may be identified and included to deepen the understanding of the intervention and its mechanisms. These cases will be identified through the quantitative component of the study, based on results that appear atypical or particularly informative in relation to the questionnaire data. This may include extreme values, as well as trajectory patterns identified through cluster-based analyses distinguishing groups with faster versus more delayed RTW processes.

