### Embedded and Iterative Integration

Qualitative and quantitative data will be analyzed in parallel and will be integrated sequentially [47]. For each RECOVA-BCS, qualitative data will be directly embedded into their corresponding quantitative dataset (Multimedia Appendix 2), which includes selected variables from the RCT, such as sociodemographic characteristics (age, occupation, company size, geographical area), RTW outcomes, care pathway indicators, and the use and perceived usefulness of intervention tools. This embedding will allow within-case comparisons and exploration of how qualitative findings relate to quantitative patterns.

Where findings converge, they will be used to strengthen the interpretation of emerging ICAMO configurations. In cases of divergence between qualitative and quantitative data, these discrepancies will be systematically documented and explored as potentially informative for refining the program theory (eg, revealing contextual contingencies or alternative mechanisms).

Integration will be conducted at the analysis level through the use of structured matrices and joint displays [47], which will allow visual and analytical comparison of qualitative and quantitative findings across cases. These tools will also be used iteratively to identify areas of convergence and divergence between datasets. Importantly, this ongoing integration will inform subsequent data collection by highlighting aspects that appear underexplored in qualitative interviews but are emerging from quantitative patterns, thereby guiding the development of additional or more focused interviews to further investigate these discrepancies.

This embedded analysis will allow for constant iteration between empirical observations and the initial program theory, progressively defining middle-range theories that hypothesize for whom, how, and under what conditions the intervention works.

Figure 2 illustrates the realist evaluation of the FASTRACS intervention processes.

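### Subgroup analyses are said to test interview-derived hypotheses, but the same RCT data may help form them and no point is stated at which they are fixed

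*Protocol article*

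**What the plan says.** The Quantitative Data Integration section gives the RCT survey data two uses. They "will be analyzed following the prespecified statistical analysis plan [25]. In addition, subgroup analyses" follow, and of these it says that "subgroup analyses (eg, by socioprofessional category, age, center, and company size) will be used to test the hypotheses developed during the interviews". The list of factors is open, and the subgroup analyses are presented as an addition to the statistical analysis plan.

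Three other places describe what else the RCT data do:

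- Study Design: "Triangulation of qualitative findings with quantitative data will allow the formulation of hypotheses on the implementation, underlying contexts, mechanisms, and effects".
- Substudy A: Trajectory Analysis (sampling), on deviant and crucial cases: "These cases will be identified through the quantitative component of the study, based on results that appear atypical or particularly informative". The section adds that clusters of faster and slower return to work may serve this purpose.
- Embedded and Iterative Integration, on how the integration feeds back into the interviews: "highlighting aspects that appear underexplored in qualitative interviews but are emerging from quantitative patterns, thereby guiding the development of additional or more focused interviews". It also states that "This embedded analysis will allow for constant iteration between empirical observations and the initial program theory".

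The Results section gives the timing. The initial substudy A sampling has been achieved, RCT follow-up ended in January 2026, data cleaning was planned for the first half of 2026, and integration is expected to begin in month 54.

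**The concern.** A test has its stated error rate only if the hypothesis was fixed without looking at the data that test it. Here the RCT data can influence a hypothesis by three routes before they are used to test it: joint formulation, selection of cases by their questionnaire results, and interviews redirected by quantitative patterns. Once a hypothesis has passed through any of these, agreement with an RCT subgroup is partly built in.

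What is at stake is the weight given to the resulting theory. The Discussion expects the study to clarify causal pathways and to inform decisions on scaling up. A chance subgroup pattern that prompted an interview theme, and was then reported as a tested hypothesis, would carry more authority in those decisions than it has earned.

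**Working it through.** **No figure to reproduce.** The article gives no significance level, RCT sample size or number of subgroup tests. The figures below are illustrations that assume a two-sided 5% level per test and independent null tests.

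**Step 1: two kinds of hypothesis.**

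| Origin | Did RCT data shape it? | Basis in the article |
|---|---|---|
| Initial interviews | No, apart from the women who belong to both datasets | Results: initial sampling achieved, integration still to begin |
| Later interviews, deviant or crucial cases, joint formulation | Yes, or possibly | Study Design; Substudy A sampling; Embedded and Iterative Integration |

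The sentence on subgroup testing does not separate the two.

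**Step 2: hypothesis taken from an RCT pattern and tested in the same data.** If the strongest of k null patterns is chosen, the test is positive whenever any of the k is positive:

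risk = 1 − 0.95^k

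- k = 4 (the number of factors named): 1 − 0.95^4 = 1 − 0.8145 = 0.1855, about 18.5%.
- k = 10 (an assumed count): 1 − 0.95^10 = 0.4013, about 40.1%.

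A simulation of 400,000 draws gave 18.5% and 40.1%. The same test in independent data gave about 5%.

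**Step 3: hypothesis from the initial interviews only.** About 20 interviewed women are also in the RCT. Let f = 20/N, where N is the number analysed (assumed, since the article does not give it). The test statistic in all N is

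z = √f · z(interviewed) + √(1 − f) · z(others)

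Suppose the hypothesis is the strongest of 4 patterns among the 20 and is tested in all N:

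| Assumed N | f | False-positive risk |
|---|---|---|
| 100 | 0.200 | 8.3% |
| 200 | 0.100 | 6.7% |
| 300 | 0.067 | 6.1% |
| 400 | 0.050 | 5.8% |

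With the 20 women left out, the risk returns to about 5%.

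**Step 4: which arms.** The Study Design section defines substudy C as analysis of questionnaires completed by the intervention group, and the sampling section for substudy C says the same. A later paragraph of Study Design brings in participants from both groups. In one arm, a difference between subgroups mixes prognosis with response to the intervention, so it cannot show that the effect of the intervention differs between them.

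**The case against.** The best defence has four parts.

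1. *The sentence covers only hypotheses developed during interviews, and the initial interview sample precedes integration.* This stands, and it limits the point. A reader might infer that every planned subgroup test is circular. The timing in the Results section does not support that, and a prior program theory, already put into intervention-context-actor-mechanism-outcome (ICAMO) form, also exists. Yet later interviews are interviews too, and nothing restricts testing to the earlier ones.

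2. *Iteration between data and theory is what realist evaluation does.* This also stands. The article says that its theories hypothesize, and that divergent findings will be documented. A reader might infer that chance patterns will be published as confirmed theory, but the article does not say so. The fault lies in using the word *test* with no stated freeze, and not in the iteration.

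3. *Multiplicity may be handled in the trial's analysis plan, which is not shown.* It may be. A reader might infer that there is no control of error at all. A condensed article cannot establish that, although presenting these analyses as additional suggests that they lie outside the plan.

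4. *The return of loop-derived hypotheses to subgroup testing is partly inferred.* Deviant cases are optional, and the further interviews are described as a way to investigate discrepancies. This is fair. The article permits the circular route but does not announce it, and nothing closes it.

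**Conclusion.** The point holds in a limited form. The article calls the subgroup analyses tests, allows the same RCT data to shape case selection, later interviews and hypotheses, and does not say when hypotheses are fixed. For a hypothesis formed or refined in that loop, the test is circular. Under the assumptions above, the false-positive risk is about 18.5% when it is the strongest of 4 patterns, against 5%. For a hypothesis from the initial interviews alone, the problem is small: 5.8% to 8.3% for an assumed 400 to 100 women analysed.

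Much larger error rates are easy to produce by assuming many factors tested at every survey wave. The article states no such number of tests, and repeated surveys of the same women are not independent, so those rates should not be attached to this study.

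The two statements about which arms substudy C uses are a separate inconsistency. It decides whether effect modification can be tested at all.

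**What to change.** 1. Before RCT outcomes are opened to the RECOVA team, deposit a dated, locked list holding the initial ICAMO theory and each interview-derived hypothesis, with its subgroup variable, outcome, time point and expected direction. Use *test* only for the entries on this list.
2. Label the subgroup analysis of any later or RCT-prompted hypothesis as exploratory. Report it as an estimate with a confidence interval, and do not count it as confirmation.
3. If RCT outcomes are already open to the team, label all these subgroup analyses exploratory.
4. Reconcile the statements that limit substudy C to the intervention arm with the one that includes both arms, and say which arms each subgroup analysis uses.

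A formal multiplicity adjustment and removal of the interviewed women are not needed to meet this point.

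The cost is a short document and a few changes of wording. The planned dates suggest a window, since integration was still to come when the article was written. The downside is that fewer findings can be presented as confirmed.

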### Embedded and Iterative Integration

Qualitative and quantitative data will be analyzed in parallel and will be integrated sequentially [47]. For each RECOVA-BCS, qualitative data will be directly embedded into their corresponding quantitative dataset (Multimedia Appendix 2), which includes selected variables from the RCT, such as sociodemographic characteristics (age, occupation, company size, geographical area), RTW outcomes, care pathway indicators, and the use and perceived usefulness of intervention tools. This embedding will allow within-case comparisons and exploration of how qualitative findings relate to quantitative patterns.

Where findings converge, they will be used to strengthen the interpretation of emerging ICAMO configurations. In cases of divergence between qualitative and quantitative data, these discrepancies will be systematically documented and explored as potentially informative for refining the program theory (eg, revealing contextual contingencies or alternative mechanisms).

Integration will be conducted at the analysis level through the use of structured matrices and joint displays [47], which will allow visual and analytical comparison of qualitative and quantitative findings across cases. These tools will also be used iteratively to identify areas of convergence and divergence between datasets. Importantly, this ongoing integration will inform subsequent data collection by highlighting aspects that appear underexplored in qualitative interviews but are emerging from quantitative patterns, thereby guiding the development of additional or more focused interviews to further investigate these discrepancies.

This embedded analysis will allow for constant iteration between empirical observations and the initial program theory, progressively defining middle-range theories that hypothesize for whom, how, and under what conditions the intervention works.

Figure 2 illustrates the realist evaluation of the FASTRACS intervention processes.

